##### Statistical analysis

Analysis will be by intention to treat. Differences between groups will be estimated using either the *t* test or Wilcoxon test at the 5% significance level to compare the distribution of the primary endpoint between the treatment samples. The patient outcome scores will be assessed with repeated measures analysis of variance (ANOVA) models to account for the repeated data collection time points. Results will be presented as an adjusted mean difference with its corresponding 95% confidence intervals.

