### Clinical study

#### Study aims

The main purpose of this study is to compare the functional and radiological results of short-stem THA using the TRI-LOCK BPS and the Minima S Femoral Stem, measured by validated clinical scores including gait analysis and standardized radiological parameters up to a minimum of 2 years’ follow-up.

The primary endpoint will be (1) the incidence of all hip-related complications up to 2 years after surgery and (2) change in health-related quality of life assessed with Western Ontario and McMaster Universities Osteoarthritis Index (WOMAC [44]) and the 36-item Health Survey (SF-36) [45] scores up to 2 years. Hip-related complications are defined as intra- and postoperative fractures, dislocation, wound infection, early or late loosening and revision surgery of any implant for any reason. The secondary endpoints at 1- and 2-years’ outcomes include hip function evaluated with the Harris Hip Score (HHS) [46], the Numeric Pain Rating Scale (NPRS), patient satisfaction [47, 48] and the parameters of gait analysis ((a) gait along a 12-m walkway at the patient’s self-selected normal speed, (b) 12-m gait at high speed in respect to patient’s functional status and (c) the Up and Go Test).

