**Fig. 5 Fig5:**
[figure not shown]
Time schedule and outcome measurements preoperatively and at 3, 6, 12 and 24 months postoperatively

The study is sponsored by the University of Patras Research Committee (ELKE) (University of Patras Campus, Rio, Greece). Ethical approval has already been obtained from the Ethics Committee of the University Hospital of Patras (approval number: 36/ 02-03-2016) and the patients’ written consent was obtained prior to participation in the study. The decision was published in the Greek Transparency Portal, called “diavgeia” on 22 April 2016, with a unique Internet Uploading Number that is ADA:6ΝΩ346906Γ-Φ6Ω. The study is registered with International Standard Randomised Controlled Trial Number ISRCTN10096716.

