#### Patient selection

Patients will be recruited from the waiting list of the senior surgeon (PM) at the Orthopedic Department of the University Hospital of Patras, Greece. Patients with unilateral hip osteoarthritis for which THA is indicated will be randomized in two different groups. The preoperative raw data will include full demographic profile, patient age, sex, body mass index (BMI), the Charlson Comorbidity Index [49] and a standardized radiological work-up. Eligible patients for short-stem implantation will be between 50 and 80 years old and suffer from (1) primary osteoarthritis, (2) inflammatory arthritis, (3) avascular necrosis and (4) post-traumatic arthritis. Exclusion criteria will include any severe comorbidities affecting functional outcome (i.e., symptomatic lumbar pathology) as well as patients with poor bone stock and any femoral deformity precluding fit and fill in the metaphysis, such in cases of hip dysplasia and severe valgus or metaphyseal deformity secondary to fracture. Participants are free to withdraw from the study at any point or a participant can be withdrawn by the investigator. If withdrawal occurs, it will be documented on a participant “Change of Status” Form. In the event of withdrawal, patients will be invited to provide final primary endpoint data.

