#### Follow-up assessments

Clinical and radiographic follow-up assessments are scheduled at 3, 6 and 12 months and annually thereafter for a minimum of 2 years’ follow-up. Each visit will include clinical and radiological examination with antero-posterior and frog-leg lateral views of the pelvis. All patients would again fill up the HHS, WOMAC, SF-36 and NPRS scale. At the 1-year appointment and yearly thereafter, patient satisfaction with the results of THA will be assessed and gait analysis will be also performed (Fig. 5).

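### Repeated measures ANOVA, as ordinarily run, leaves out randomised patients with a missed visit, which sits poorly with intention to treat, and the adjusted mean difference has no named time point

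*Protocol article*

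**What the plan says.** All references are to the clinical study in the protocol article.

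- **Analysis set** (Statistical analysis): "Analysis will be by intention to treat".
- **Primary endpoint test** (same section): a t test or "Wilcoxon test at the 5% significance level to compare the distribution of the primary endpoint between the treatment samples".
- **Scores** (same section): "The patient outcome scores will be assessed with repeated measures analysis of variance (ANOVA) models to account for the repeated data collection time points".
- **Reported estimate** (same section): "Results will be presented as an adjusted mean difference with its corresponding 95% confidence intervals". No time point, contrast or adjustment variable is given.
- **Endpoint** (Study aims): the second part of the primary endpoint is change in WOMAC "and the 36-item Health Survey (SF-36) [45] scores up to 2 years".
- **Occasions** (Fig. 5 caption): "Time schedule and outcome measurements preoperatively and at 3, 6, 12 and 24 months postoperatively", which is five occasions, four of them after surgery. The Follow-up assessments section agrees.
- **Withdrawal** (Patient selection): "Participants are free to withdraw from the study at any point or a participant can be withdrawn by the investigator". Patients who withdraw are asked for final primary endpoint data.
- **Sample size** (Power and sample size calculation): 45 per group for 80% power at an effect size between 0.25 and 0.6, with no allowance for loss stated.

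**The concern.** Classical repeated measures ANOVA works on a complete set of scores per patient. A patient who misses one questionnaire then drops out of the analysis, together with every score already collected. If this happens, the analysis is of completers, not of all randomised patients. A final score obtained from a withdrawing patient would go unused if an intermediate visit was missed. The comparison loses precision, and it may be biased if completers differ from the rest.

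The second difficulty is what gets reported. WOMAC and SF-36 fall under two sentences of the same section: the t or Wilcoxon test, because they belong to the primary endpoint, and the ANOVA, because they are patient outcome scores. Nothing says which governs. The one adjusted difference could be a group main effect averaged over occasions or a contrast at one visit, and these can differ widely.

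**Working it through.** **1. Reproducing the planned size.** Inputs: 45 per group, 80% power, 5% level (Power and sample size calculation; Statistical analysis). Assumptions: two-sided test, and effect size read as a difference in SD units. The noncentral t calculation at 0.6 SD requires 44.6, so 45 per group. Power is 80.4% at 45 and 79.5% at 44. The planned number is therefore reproduced at the upper end of the stated effect range only, for two groups compared at one time with no missing data. It has no reserve.

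**2. Complete cases.** The documents give no missingness rate, so I assume a probability p of missing each of the four postoperative visits, independent between visits, with the preoperative score always present. The complete fraction is (1 − p)^4.

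- p = 3%: 0.97^4 = 0.885; 45 × 0.885 = 39.8 per group
- p = 5%: 0.95^4 = 0.815; 45 × 0.815 = 36.7 per group
- p = 10%: 0.90^4 = 0.656; 45 × 0.656 = 29.5 per group

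Using all available 24-month scores instead leaves 45 × (1 − p) = 43.7, 42.8 and 40.5 per group.

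**3. Power for a single-time-point two-sample t test at 0.6 SD.**

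| Missed per visit | Complete cases per group | Power | Available at 24 months per group | Power |
|---|---|---|---|---|
| 3% | 39.8 | 75% | 43.7 | 79% |
| 5% | 36.7 | 72% | 42.8 | 78% |
| 10% | 29.5 | 62% | 40.5 | 76% |

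At 10%, the fall from 80% to 76% comes from the missing 24-month scores themselves. The further fall to 62% comes from discarding incomplete patients.

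**4. What a group main effect would estimate.** Let D be the stem difference at 24 months, with no difference before surgery. The main effect is the plain average over the occasions included.

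- Constant D after surgery: (0 + D + D + D + D)/5 = 0.80 D with the preoperative score as a level; 1.00 D over the four postoperative occasions.
- Growing linearly with time to D: (0 + 0.125 + 0.25 + 0.5 + 1)D/5 = 0.375 D; 0.47 D over four.
- Present only at 24 months: D/5 = 0.20 D; 0.25 D over four.

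The main effect equals the 24-month difference only if the difference is constant after surgery and the preoperative score is not a level.

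**The case against.** A reader might infer that the protocol contradicts itself by excluding incomplete patients. It does not say so. Its wording could loosely cover a likelihood-based model, or ANOVA after imputation, and missing-data handling may sit in a full protocol or analysis plan that is not shown. What stands is a conflict that depends on how the named method is run.

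A reader might also infer that the trial will report the overall group effect in place of the 2-year difference. The text commits to neither. A group-by-time term or a 24-month contrast fits the wording, and the endpoint is defined up to 2 years, not at 2 years. The shrinkage in step 4 is therefore conditional on one reading.

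The t or Wilcoxon test softens the point: applied to one visit, it does not remove a patient for missing an earlier one. Asking withdrawing patients for final data also helps. Neither settles which analysis governs WOMAC and SF-36 or when the adjusted difference is taken.

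The power figures in step 3 are for a single-time-point comparison, not for an averaged ANOVA effect. For a constant 0.6 SD difference averaged over four postoperative visits, with an assumed correlation between visits of 0.3 to 0.7, complete-case power is higher: 85–97%, 82–96% and 73–91% at 3%, 5% and 10% missed. If misses cluster in the same patients, fewer are lost at the same per-visit rate. Finally, it is tempting to add that the method assumes equal correlation between visits. That does not apply to the between-group effect, which is a comparison of patient means.

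**Conclusion.** The point holds in a limited form. The named method, as ordinarily run, leaves out randomised patients with any missed score. This fits poorly with intention to treat, with permitted withdrawal and with a sample size that has nothing to spare. Separately, the primary scores have two analyses with no stated precedence, and the single adjusted difference has no time point.

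The size is illustrative. Under independent misses of 3% to 10% per visit, about 5 to 15 of 45 patients per group would be left out. For a single-time-point comparison at 0.6 SD, that costs roughly 4 to 14 percentage points of power relative to using all available 24-month scores (79 − 75 = 4; 76 − 62 = 14). If the group main effect is read with the preoperative score as a level, a constant postoperative difference shrinks to 4/5. Missingness rates, their independence and the main-effect reading are assumptions, not statements in the protocol. The change is worth making because a better-specified method is available for a change of wording.

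**What to change.** Analyse the scores with a likelihood-based mixed model for repeated measures:

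- include all randomised patients with any postoperative score, in their allocated group;
- fit visit as categorical, with stem-by-visit and baseline score terms, and use the preoperative score as a covariate, not as an outcome level;
- name the 24-month stem contrast, with its 95% confidence interval, as the adjusted mean difference;
- state that this model replaces the t or Wilcoxon test for WOMAC and SF-36;
- specify the covariance structure in advance, with a simpler fallback if an unstructured one does not converge.

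The cost is analysis wording, with no new patients, visits or data. The downside is small: the model is valid only if scores are missing at random given what was observed, and the covariance structure becomes one more choice to fix before analysis.

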#### Randomization procedures

We used stratified block randomization consisting of a random sequence of blocks of 10 consecutive surgical procedures each. Randomization was performed in the operating theater, after anesthetic induction and just before incision, using a sequentially numbered opaque sealed envelope.

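### The tests named for the primary score comparison do not give the promised adjusted mean difference, and the preoperative score is not named as a covariate, which costs precision

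*Protocol article*

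**What the plan says.** The clinical Study aims section gives the primary endpoint two parts. The first is a proportion: "The primary endpoint will be (1) the incidence of all hip-related complications up to 2 years after surgery". The second is a score: "change in health-related quality of life assessed with Western Ontario and McMaster Universities Osteoarthritis Index" together with the SF-36, up to 2 years. This point concerns the second part only.

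The Statistical analysis section of the clinical study makes three statements that bear on the scores:

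- For the primary endpoint: "Differences between groups will be estimated using either the *t* test or Wilcoxon test at the 5% significance level".
- For the scores over time: "The patient outcome scores will be assessed with repeated measures analysis of variance (ANOVA) models to account for the repeated data collection time points".
- For reporting: "Results will be presented as an adjusted mean difference with its corresponding 95% confidence intervals".

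The article names no adjustment variable. Two candidates exist in the design. Preoperative values are collected, as the Fig. 5 caption shows: "Time schedule and outcome measurements preoperatively and at 3, 6, 12 and 24 months postoperatively". The allocation was also stratified, according to Randomization procedures: "We used stratified block randomization". That section gives a block size of 10 but does not name the stratification factors.

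**The concern.** The analysis and the estimate to be reported do not match. Someone following the section literally would run a t test or Wilcoxon test on the change scores and then find that neither supplies the adjusted figure to be reported. The ANOVA could supply one, but its only stated purpose is to handle the repeated visits. Two analyses therefore compete for the same scores, and the adjustment could be chosen after the data are seen.

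There is also a question of efficiency. A change score subtracts the whole baseline value, whereas a covariate model subtracts only the share that predicts follow-up. When r is below 1, subtracting the whole baseline adds noise. The stated sample size has little room for that, because it reaches 80% power only at the top of the effect range given in Power and sample size calculation.

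**Working it through.** **Inputs from the protocol article.** 45 patients per group, power of 80% or better, and a standardised effect between 0.25 and 0.6 (Power and sample size calculation); 5% significance level (Statistical analysis).

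**Assumptions.** Two-sided test; equal SDs before surgery and at follow-up; baseline to follow-up correlation r of 0.3, 0.5 or 0.7. The article states none of these. It also does not say whether its standardised effect is in units of the change-score SD or the follow-up SD, so both are shown.

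**Step 1. Reproduce the plan's figure.** For an unadjusted comparison, n per group = 2(1.960 + 0.842)² / d². At d = 0.6 this is 43.6, so 44 per group. The exact t test gives 44.6, so 45. Power at 45 per group is 81.2% by the normal approximation and 80.4% by the exact t test. The stated size is thus reproduced at d = 0.6 by an unadjusted test and does not rely on covariate adjustment.

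**Step 2. Variances.** In units of the score variance, per patient:

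- change score: 2(1 − r)
- ANCOVA on the preoperative score: 1 − r²
- ratio of ANCOVA to change: (1 − r²) / [2(1 − r)] = (1 + r)/2

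**Step 3. Power with 45 per group.** Power = Φ(0.6 × √(45/2) / √v − 1.960) = Φ(2.846/√v − 1.960), where v is the variance relative to the one on which d = 0.6 is scaled.

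| Assumed r | Ratio (1+r)/2 | d on change SD: change score | d on change SD: ANCOVA | d on follow-up SD: change score | d on follow-up SD: ANCOVA |
|---|---|---|---|---|---|
| 0.3 | 0.65 | 81% | 94% | 67% | 85% |
| 0.5 | 0.75 | 81% | 91% | 81% | 91% |
| 0.7 | 0.85 | 81% | 87% | 96% | 98% |

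Example at r = 0.3 with d on the change SD: 2.846/√0.65 − 1.960 = 1.570, and Φ(1.570) = 0.942. With d on the follow-up SD, v is 1.4 for change and 0.91 for ANCOVA, giving 0.672 and 0.847.

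**Step 4. The same gain as patients.** With d on the change SD, 80% power needs 43.6 × ratio per group: 29, 33 and 38 at r of 0.3, 0.5 and 0.7, against 44 for the unadjusted change score.

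**Step 5. Strata.** No gain can be computed, because the factors are not named. Adjusting for them tightens the interval only to the extent that they predict the score.

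**The case against.** The strongest reply is that the promise of an adjusted difference directly follows the sentence on repeated measures ANOVA, so the natural reading is that those models supply it. They can give model-based mean differences with confidence intervals and can take covariates. A covariate list is also something that a condensed article may leave to an analysis plan. This reply stands against two stronger readings that a reader might infer:

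- **That the adjusted difference cannot be produced.** The text leaves it undefined, not impossible.
- **That the baseline score is unused.** A change score uses it by subtraction, and the ANOVA may include the preoperative visit as a time level. What is not stated is its use as a covariate.

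The reply does not remove the mismatch. The article itself names the t test or Wilcoxon test for the primary endpoint, and neither gives an adjusted mean difference. A later plan that made a covariate model primary would depart from that choice. One that kept the named tests could not deliver the promised estimate from them.

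Three further objections limit the point:

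- A t test on change is unbiased under randomisation.
- The power gain depends on r and on the scale of the effect. With r = 0.7 and the effect on the follow-up SD it is only 96% to 98%. A reader might infer from the 67% cell that the planned test is underpowered at d = 0.6, but that cell needs both r = 0.3 and the follow-up scale, and the article states neither.
- The variance comparison is with a test on change at a single visit, not with the repeated measures model.

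**Conclusion.** The point holds as a mismatch between the named tests and the promised estimate, together with an avoidable loss of precision. Neither test named for the primary endpoint yields the adjusted mean difference, and the ANOVA has no stated covariate.

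Against an unadjusted change score, adjusting for the preoperative score would cut the variance by 35%, 25% or 15% at assumed r of 0.3, 0.5 or 0.7. The power gain ranges from about 2 to 18 percentage points over the values of r and the two scales examined. The direction is certain for any r below 1 with equal SDs; the size is not, because the article gives neither r nor the scale of its effect.

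This is a matter of efficiency and clarity, not validity. It covers only WOMAC and SF-36. Complication incidence is a separate primary component to which a mean difference does not apply, so it would be wrong to treat score change as the whole primary endpoint.

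**What to change.** Name one primary model for each score, adjusted for the preoperative score and the randomisation strata. Either of these would do:

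- ANCOVA of the 24-month score on stem group; or
- a repeated measures model of the 3, 6, 12 and 24-month scores, with the 24-month group contrast as the primary estimate. This keeps the earlier visits in the analysis.

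State that the reported adjusted mean difference and its 95% CI come from this model. Keep the t test or Wilcoxon test on change as a sensitivity analysis. The sponsor must first name the stratification factors, since the model cannot be fully specified from the article without them.

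The cost is a change to the analysis wording, best made before outcomes are compared by group. No new data, visits or patients are needed.

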## Discussion

As THA is increasingly being performed in patients who are younger and more active, the need for better implant design for bone and soft tissue preservation is mandatory; short, uncemented femoral implants are an alternative considering that they provide the following theoretical advantages [62–68]: (1) demonstrate more physiological load transfer distribution to the proximal femur, reducing proximal stress shielding, (2) facilitate minimally invasive surgical techniques, (3) preserve metaphyseal bone stock by a more proximal fixation, (4) provide more favorable conditions in the potential revision setting, (5) are viable alternatives in cases of metaphyseal-diaphyseal mismatch (e.g., excessively bowed femurs, deformed bones, narrow Dorr Type A diaphysis) and (6) have decreased rates of thigh pain.

The fact is that all the above benefits still need to be sufficiently validated and also short stems should provide better or, at least equal outcomes compared to those already have been reported for standard stems in long-term clinical studies. One major problem is that there are several variations and design philosophies of short stems in the market and their types and categories are sparse and unclassified [69, 70]. Recently, Gómez-García et al. [71] published a detailed classification of short stems by means of a nomenclature that describes them accurately, taking into consideration several variables, such as (1) the anatomical region that they occupy or invade, (2) basic geometric design, (3) main stress distribution zones, (4) bone resection level and (5) the orientation axes used for insertion. According to this classification, which we have adopted, the Tri-Lock BPS and Minima S stems are classified as short stems type C, which means that they occupy the cervico-metaphyseal-diaphyseal area. The Tri-Lock BPS stem is further classified as a straight, wedged stem with major stress transmission areas, the calcar and the diaphysis and a rectangular cross-section and the Minima S stem as a curved, wedged stem with calcar and proximal diaphyseal loading distribution and an oval-trapezoidal cross-section.

In our study, we aim to conduct a comprehensive assessment, by means of a comparative clinical study as well as biomechanical testing and FEA of two different short femoral stems, which are theoretically classified in the same main category. For this reason, we decided to compare a newly introduced short stem, Minima S, for which clinical performance data are lacking with an older generation short stem, Trilock BPS, with an established performance record in short to midterm follow-up [72–74]. We can hypothesize that even these subtle variations in geometric design between these two stems, which are classified within the same subgroup, may create different loading characteristics and thus dissimilar biomechanical behaviors, which in turn could have an influence to their clinical performance. Consequently, if this scenario is finally confirmed, the conclusions of the present study could not be extrapolated to all short stems even if they belong to the same category.

Today’s demographic profile and demands of patients for hip replacement surgery emphasizes the importance of using more accurate assessment tools that can detect changes in functional ability. Despite the fact that patient-reported outcomes measures (PROMs) are widely used in the literature to assess outcome following total hip arthroplasty, they represent only a self-reported perception of a patient’ s functional status and are subject to patient reporting bias. Furthermore, several PROMs suffer from a ceiling effect [75], which means that a substantial proportion of participants reach the maximum score at the same period and thus the extent of a possible further improvement may not be determined. Hence, in our study we decided to include an objective tool supplementary to PROMs for the assessment of functional ability after THA, that is the gait analysis using an inertial sensor. Despite the fact that stereophotogrammetric systems are considered the gold standard for clinical gait analysis, they require a specially equipped laboratory and they are time-consuming and expensive. More recently, inertial sensors have developed as reliable tools alternative to stereophotogrammetric systems and have also demonstrated responsiveness to postoperative changes in patients with hip osteoarthritis [60, 76].

